##### Sample size

The primary outcomes are a diagnosis of depression according to PRIME-MD and severity of depression according to the HDS and GDS. In a recent meta-analysis, the average effect size for CBT (including PST trials) was 1.06 and for PST was 1.00 [10]. To be conservative, we have used the smaller ES of 1.00. According to G-power, we would need only 25 participants per group have 95% power to detect a significant difference (p < 0.05) between the 2 active treatments and the control condition [53]. However, we are also interested in the relative efficacy of each of the 2 interventions. Given that these two treatments have never been compared in any clinical setting, we determined that to be conservative, we should power the study to identify even small differences in effect sizes (Cohen’s D = 0.25) between the two treatments. In order to be able to observe a difference between the two groups of 0.25 with 80% power and a significance level of 0.05, we need 59 participants per group. That is, 177 participants in total.

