**Methods/design:**

The PROMISE-D study is a randomised controlled trial of two evidence-based treatments for late-life major or minor depression for patients who also have at least one co-morbid chronic health problem. Participants will be randomised to two active interventions (PST or CBT) or enhanced treatment-as-usual (E-TAU). Primary outcomes will be depression diagnostic status and severity of depression (according to the Hamilton Depression Rating Scale and the Geriatric Depression Scale). Secondary outcomes will be anxiety severity, quality of life and health care utilisation. Assessments will be conducted by a researcher who remains blind to the patient’s treatment allocation and will be conducted pre and post-treatment and at six and 12 months follow-up. Health care utilisation will be assessed throughout a two year period following entry to the trial. Executive function, rumination and emotion regulation will also be measured to determine the impact of these factors on treatment response in two treatment groups.

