### Aims and hypotheses

Although there have been numerous trials of psychological interventions for patients with late-life depression in the past decade, there continue to be major gaps in the literature. Firstly, few studies aim to treat depression in the context of ill health, despite the fact that many older adults have both depression and one or more chronic physical illnesses. There are also few studies that compare different psychotherapies for late-life depression. The PROMISE-D trial aims to bridge these gaps. Specifically, the aim of the study is to evaluate two psychological therapies (PST and CBT), both of which are definitely efficacious for the treatment of late-life depression, for patients with one or more co-morbid physical illness.

We hypothesise that PST and CBT will be superior to a wait-list control group in the treatment of depression for patients with co-morbid health problems. We also aim to determine what baseline characteristics might best predict outcome in each treatment condition. Based on the hypothesised mechanisms of PST, we expect that patients with executive dysfunction (poor score on the Stroop Interference Task [37]) will respond better to PST than CBT [16]. In contrast, we expect patients with excessive rumination (measured by the Ruminative Response Scale; RRS [38]) and patients with affective dysregulation (measured by the Emotion Regulation Questionnaire; ERQ [39]) to respond better to CBT than PST [39,40].

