### Outcome measures

The primary outcome will be diagnoses of depression according to the PRIME-MD Depression module. In order to allow for multi-modal assessment we will also measure participants’ depression using the GDS-SF [43] and clinician-rated severity according to the HAM-D [45]. Two secondary outcomes will be measured. Quality of life will be assessed with the SF-36 [46] and anxiety will be measured using the Geriatric Anxiety Inventory [47]. These assessments will be conducted by a researcher who remains blind to the participant’s treatment allocation. Blindness will be confirmed by having the independent researcher guess the group that they think each participant belongs to at the end of the treatment period.

As we are interested in which factors affect treatment success, we will also be taking a number of process measures. Executive function will measured using the Stroop Interference Task [37]. For logistical reasons only participants in PST and CBT conditions will be administered the Stroop task because it requires face-to-face administration. The Stroop will be used as a predictor of treatment outcome and not an outcome measures. All participants will be assessed for level of rumination (via the Ruminative Response Scale [38]) and affective regulation (via the Emotion Regulation Questionnaire [39]).

Additionally, demographic variables such as ethnicity and level of education will be recorded, as well as more specific information about previous depressive diagnoses and treatment. In order to confirm details of their chronic illness(es), RCT participants will also be asked to consent to the research team accessing their medical files.

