#### Statistical analysis

There are 4 measurement times, of which 3 are post-intervention. Linear mixed models will be used to account for the hierarchical, non-independent nature of the data: repeated measures on patients nested within clusters (primary care services). Baseline outcome measures (e.g., HAM-D and GDS-SF) will be used as a covariate, which improves efficiency [52]. These models will allow for 1) comparing patterns of change over time by testing the intervention group by time interaction and 2) estimating and testing differences in outcome measures between groups at time points of interest via linear contrasts. Reporting will follow the CONSORT statement [41].

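### The article names one primary outcome in Outcome measures but three in the Abstract and the sample-size text, so it does not fix which result decides the trial

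*Protocol article*

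**What the plan says.** Three places in the protocol article define the primary outcome.

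- Outcome measures: "The primary outcome will be diagnoses of depression according to the PRIME-MD Depression module". The next sentence adds the severity measures in a different role: "In order to allow for multi-modal assessment we will also measure participants’ depression using the GDS-SF", together with the clinician-rated HAM-D. The section then lists two secondary outcomes, quality of life and anxiety. The GDS-SF and HAM-D are therefore neither called primary nor listed as secondary.
- Abstract, Methods/design: "Primary outcomes will be depression diagnostic status and severity of depression", with severity measured on the Hamilton scale and the Geriatric Depression Scale.
- Analysis, second Sample size paragraph: "The primary outcomes are a diagnosis of depression according to PRIME-MD and severity of depression according to the HDS and GDS". I take HDS to mean the HAM-D and GDS to mean the GDS-SF.

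The comparisons come from two places. Aims and hypotheses gives two: "We hypothesise that PST and CBT will be superior to a wait-list control group" (the control arm is E-TAU elsewhere). The second Sample size paragraph adds CBT versus PST: "However, we are also interested in the relative efficacy of each of the 2 interventions". Statistical analysis specifies linear mixed models over four measurement times, three of them post-intervention, with a group-by-time test and "estimating and testing differences in outcome measures between groups at time points of interest via linear contrasts". Those time points are not named. The only significance level in the article is 0.05, and it appears only in the two sample-size paragraphs.

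**The concern.** Which outcome is primary is a protocol-level decision. Here it is stated in two incompatible ways, and an analysis plan that is not shown cannot remove a contradiction within the published text.

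If the diagnosis result is null and the HAM-D result is positive, the trial has missed its primary outcome under Outcome measures, but has a positive primary outcome under the Abstract and the sample-size text. The choice between these readings could be made after the data are seen. The same freedom extends to the contrast and the time point. Strengths of the study treats short-term and long-term efficacy as different questions, because GPs can act on a depression diagnosis after the treatment phase, so the choice of time changes what is tested. The answer has practical weight: under Challenges, the investigators offer to train practice psychologists in whichever therapy comes out best.

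There is also a mismatch of type. The sole primary outcome in Outcome measures is a yes/no diagnosis. The sample size is in units of Cohen's d, and the model is linear with baseline scale scores as example covariates. The design arithmetic and the analysis are thus written for the two scales that Outcome measures does not call primary.

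**Working it through.** **The plan's own figures.** The article states no family-wise error rate, so there is none to reproduce. Its sample-size figures are all for differences in means, n = 2(z₁₋α/₂ + z_power)²/d² per group:

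- d = 1.00, 95% power, two-sided 5%: 2(1.960 + 1.645)² = 26 (27 by t-test). The stated 25 is within two patients.
- 47/(1 − 0.20) = 58.75, so 59. This reproduces.
- d = 0.25, 80% power: 2(1.960 + 0.842)²/0.0625 = 252, against the stated 59. This does not reproduce. It is a separate problem, relevant here only because the power statement has to be revisited anyway.

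None of these is a calculation for a proportion with a diagnosis.

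**Counting the possible tests.** Outcomes: 1 (Outcome measures) or 3 (Abstract, second Sample size paragraph). Contrasts: 3. Post-intervention times: 3. The largest family is 3 × 3 × 3 = 27.

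**Chance of at least one false positive.** Assumptions: three equal arms, every null true, each test two-sided at an unadjusted 5%. Treating 27 tests as independent gives 1 − 0.95²⁷ = 0.75. The three contrasts share arms, and outcomes and times are correlated, so the rates below come from simulation (200,000 runs per setting). The article gives no correlations; those used are assumptions from 0 to 0.9.

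| Family | Tests | Chance of ≥ 1 false positive |
|---|---|---|
| 1 outcome, 1 time, 3 contrasts | 3 | 0.12 |
| 3 outcomes, 1 time, 3 contrasts | 9 | 0.20–0.32 |
| 1 outcome, 3 times, 3 contrasts | 9 | 0.19–0.32 |
| 3 outcomes, 3 times, 3 contrasts | 27 | 0.30–0.69 |

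For the 27-test family, with the same correlation between outcomes and between times, the rate is 0.69 at 0, 0.58 at 0.5, 0.46 at 0.7, 0.39 at 0.8 and 0.30 at 0.9.

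**If the therapies work as the sample size assumes.** With d = 1.00 for both against control, only CBT versus PST can give a false positive. At correlations of 0.4 to 0.8 the chance is 0.18–0.32 over its nine tests (3 outcomes × 3 times) and 0.10–0.13 over three outcomes at one time. It is 0.05 for one outcome at one time.

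**Price of a binary primary outcome.** Assume diagnosis is a normal severity score cut at a threshold, with 47 analysed per group. With a proportion p_C of controls still depressed, the treated proportion is p_T = Φ(Φ⁻¹(p_C) − d), and power = Φ{(p_C − p_T)/√[(p_C(1 − p_C) + p_T(1 − p_T))/47] − 1.96}.

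- d = 0.5 (my illustration), p_C = 0.5: p_T = 0.309, and 0.191/0.0993 − 1.96 = −0.03, so power is 0.49. At p_C = 0.6 it is 0.50 and at 0.8 it is 0.44. As a score: Φ(0.5√(47/2) − 1.96) = Φ(0.46) = 0.68.
- d = 1.00, p_C from 0.5 to 0.8: 0.97–0.98, against Φ(4.85 − 1.96) = 0.998 as a score.

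**The case against.** The strongest objection concerns how far the multiplicity argument can be taken. A reader might infer that success may be claimed on any of 27 tests, each at 5%, so that a false-positive primary result is about as likely as not. The article does not support that. Its 0.05 belongs to the sample-size calculations, and Statistical analysis states no alpha. No passage declares all outcomes, contrasts and times primary, or says that any one of them suffices. A testing rule and a primary time point could properly sit in a full protocol or analysis plan that is not shown, and their absence from a condensed article is not itself a fault. A rate near one half needs the largest family, assumed correlations around 0.5 to 0.7 and no treatment effect anywhere. That last condition contradicts the article's own planning effect of 1.00 against control. This part of the objection stands, and the error rates above are conditional illustrations only.

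A second objection is that choosing the diagnosis at post-treatment is not simply restoring what Outcome measures says. That section names no primary time, and long-term efficacy is a stated purpose of the trial. One severity scale would serve equally well as the single primary outcome. This also stands and shapes the remedy.

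Neither objection touches the contradiction between one primary outcome and three.

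**Conclusion.** The contradiction is established on the face of the article and must be resolved: one primary outcome in Outcome measures, three in the Abstract and the second Sample size paragraph, and no statement of which prevails. It could reverse the trial's primary conclusion whenever diagnosis and severity disagree.

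The size of the accompanying error-rate problem depends on what is finally declared primary. Even the narrowest reading, one outcome at one time with three unadjusted contrasts, would carry about 0.12 rather than 0.05. The wider families rest on assumed correlations, a global null and unadjusted testing, so they show what the ambiguity would permit rather than what the plan prescribes.

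**What to change.** 1. State the same single primary outcome, at one named time point, in the Abstract, Outcome measures and the second Sample size paragraph. List the other depression measures and the other times as secondary.
2. State the order of testing for that outcome: a global three-arm test at 5%, then the pairwise contrasts at 5% each only if it is significant. With exactly three arms this holds the family-wise error at 5%. If all arms are equal, the global test errs 5% of the time; if only two are equal, a single true null remains, tested at 5%.
3. If PRIME-MD diagnosis is kept, specify a model for a binary outcome and restate the power for proportions. If one severity scale is chosen, the linear mixed model can stay and Outcome measures must change.

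**Cost.** No extra patients are needed for the comparisons with control at the planned d = 1.00. Even the stricter Bonferroni level of 0.05/3 = 0.0167 leaves Φ(4.85 − 2.39) = 0.99 power with 47 analysed per group. The measures not chosen can no longer carry the primary claim. Choosing diagnosis is more than a wording change: the model and power statement need rework, and power is lower than for a score, slightly at d = 1.00 and substantially at smaller effects. The CBT versus PST comparison is weak either way: as a score with d = 0.25 and 47 per group, power is 23% at 5% and 12% at 0.0167.

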**Discussion:**

Multi-morbidity, the experience of two or more chronic health problems, is becoming an increasing problem internationally, particularly amongst the elderly. Evidence-based psychological treatments exist for late-life depression and these have been shown to be effective for participants with individual health problems and depression. However, there are no studies that have compared the two leading psychotherapies shown to be effective in the treatment of late-life depression. In addition, many trials of psychotherapy with older adults exclude those with multi-morbidity. Hence, this trial will confirm whether CBT and PST are efficacious in the treatment of depression in the context of complex medical needs and determine which of these two interventions is most efficacious.

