### Analysis

#### Sample size

177 participants will be recruited to the RCT. In order to achieve 95% power and α = 0.05, 47 participants per group are needed. Allowing for 20% attrition, this requires 59 participants per group.

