### Challenges

We envisage that the greatest challenge in this trial will be recruiting the sample. There are a number of potential barriers to recruitment in this study. Firstly, recruiting busy GP practices to take part in this study may prove challenging. However, we have designed the PROMISE-D trial to require minimal input from surgeries, such that they need only hand out a single form to all people over 65. Involvement in the trial will result in considerable benefits to older patients with multi-morbidity, a group that is particularly difficult to treat. The benefits include screening for depression and treatment of depression (in 66% of cases) without cost to the patient or GP. We have also agreed to offer free training to the psychologists attached to any GP surgeries at the end of the trial in whichever intervention proves most efficacious. This will also ensure long-term implementation of effective psychological care for these patients.

There are also barriers to recruitment of this particular patient group. Older people with chronic physical illnesses and depression may be difficult to recruit because motivation may be problematic, as related to their mood difficulties. Furthermore, mobility issues may also compromise their ability to attend sessions. To deal with these issues we will attempt to see patients in their GP surgery to minimise travel and have some funding to compensate participants for direct travel costs, where necessary.

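### The stated 80% power for d = 0.25 between CBT and PST is wrong: 59 per group gives about 27% in the comparison described, and the baseline-adjusted model does not plausibly reach 80%

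*Protocol article*

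**What the plan says.** The article has two paragraphs headed Sample size.

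- The first, directly under Analysis, works at 95% power and α = 0.05 and says "47 participants per group are needed. Allowing for 20% attrition, this requires 59 participants per group". It names no effect size and no comparison.
- The second, under Statistical analysis, first finds 25 per group sufficient for active treatment against control (effect size 1.00, 95% power). It then sets the trial's size by CBT against PST, with Cohen's d = 0.25 as the small difference to be identified: to "observe a difference between the two groups of 0.25 with 80% power and a significance level of 0.05, we need 59 participants per group". The total follows: "we need 59 participants per group. That is, 177 participants in total". Attrition, covariate adjustment and repeated measures play no part in this calculation.

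The Statistical analysis section plans linear mixed models with the baseline score as covariate, three post-intervention assessments, and clustering by primary care service. It gives no correlation.

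The head-to-head question is a stated purpose. The Discussion part of the abstract says the trial will "determine which of these two interventions is most efficacious", the Conclusion returns to the same question, and the Challenges section offers practices' psychologists training "in whichever intervention proves most efficacious".

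**The concern.** A standardised difference of 0.25 is small, and a comparison of two independent groups normally needs some hundreds per group to detect it at 80% power. Fifty-nine is far too few, and the article states nothing that would close the gap.

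The number also appears with two incompatible meanings. In one paragraph 59 is a recruitment target that already allows for dropout, at 95% power. In the other it is the number needed, with no allowance for dropout, at 80% power.

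This is the printed reason for the sample size, and it concerns the comparison that the article presents as new. A reader told that power was 80% for a small difference could take a non-significant CBT–PST contrast as good evidence that no such difference exists. With the real power, that inference would be unsafe.

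**Working it through.** **Inputs from the article:** d = 0.25, power 80%, α = 0.05 (second Sample size paragraph); 59 per group, three equal groups, 177 in total; 20% attrition and 47 per group (first Sample size paragraph). Sidedness is not stated; two-sided is taken, with one-sided also shown.

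**1. The article's other figures.**
- Attrition: 47 / 0.8 = 58.75, so 59. This step is correct.
- Active against control, effect size 1.00, 95% power: n = 2 × (1.960 + 1.645)² / 1.00² = 26.0 per group (27 by the t-test). The stated 25 is roughly right and is not challenged.

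**2. Required number for d = 0.25 at 80% power.**
- n = 2 × (z₁₋α/₂ + z₀.₈)² / d² = 2 × (1.960 + 0.842)² / 0.0625 = 251.2, so 252 per group. The noncentral t gives 252.1, so 253.
- One-sided: 2 × (1.645 + 0.842)² / 0.0625 = 197.8, so 198 (199 by the t-test).
- With 20% attrition the two-sided number is 253 / 0.8 = 316.25, so 317 per group.
- The stated 59 is 59 / 253 = 23% of the two-sided requirement.

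**3. Power at the stated size.** Power ≈ Φ(d√(n/2) − 1.96).
- n = 59: Φ(0.25 × √29.5 − 1.96) = Φ(−0.60) = 27% (noncentral t 27.0%; one-sided 38%).
- n = 47: Φ(0.25 × √23.5 − 1.96) = Φ(−0.75) = 23% (noncentral t 22.4%; one-sided 33%).
- Difference detectable with 80% power, two-sided: d = 0.52 at n = 59 and 0.58 at n = 47.

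**4. Could 0.25 have been meant as Cohen's f?** That is d = 0.50 for two groups and needs 64 per group. A three-group analysis of variance with f = 0.25 needs 157.2 in total, about 53 per group. Neither gives 59.

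**5. Gain from the planned model.** The correlation r is assumed, because none is given. The same r is used between all pairs of assessments, and clustering is ignored.
- Baseline-adjusted, one time point: variance factor 1 − r².
- Baseline-adjusted mean of three post-treatment scores: variance factor (1 + 2r)/3 − r².

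| Assumed r | One time point, n = 59 / 47 | Mean of three, n = 59 / 47 |
|---|---|---|
| 0.3 | 29% / 24% | 52% / 44% |
| 0.5 | 34% / 28% | 55% / 46% |
| 0.7 | 47% / 39% | 68% / 58% |

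For 80% power the variance factor must fall to n / 251.2:
- n = 59: factor 0.235, so r of about 0.87 (one time point) or 0.79 (mean of three).
- n = 47: factor 0.187, so r of about 0.90 or 0.84.

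**6. The two derivations of 59.**

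| | First Sample size paragraph | Second Sample size paragraph |
|---|---|---|
| Power | 95% | 80% |
| Effect size | not given | d = 0.25 |
| Attrition | 20%, included in 59 | none |
| Needed before attrition | 47 | 59 |

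Both cannot describe the same calculation.

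**The case against.** **The article plans a better analysis than an unadjusted t-test.** This stands in part. Baseline adjustment and three post-treatment assessments raise power, and a mixed model keeps partial follow-up from people who later drop out, so the n = 47 figures are somewhat pessimistic. A reader might infer from 27% and 22% that a true difference of 0.25 would be missed about three times in four. That holds only for an unadjusted comparison at one time point. Over the assumed range of correlations, the planned model misses it between about 32% (100 − 68) and 76% (100 − 24) of the time. It still falls short of 80%, and clustering by practice could take back some of the gain.

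**The trial can still compare the therapies.** This stands. A reader might infer that it cannot say which therapy is better. The article does not support that, since unadjusted power is 80% for differences of 0.52 to 0.58. What fails is the claim about a small difference.

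**The main hypothesis is unaffected.** This also stands. The hypothesis under Aims and hypotheses is superiority of both therapies over control, and at the article's assumed effect size of 1.00 that comparison has ample numbers.

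**The origin of 59 is unknown.** It is tempting to say that 59 was computed for d = 0.75 and then attached to 0.25, because 47 per group gives 94.9% power at d = 0.75 and 47 / 0.8 rounds to 59. That is conjecture, as the first paragraph gives no effect size. Another route comes nearly as close. A repeated-measures interaction with f = 0.125, two groups, four times and an assumed correlation of 0.5 needs 45 per group for 80% power, and 45 / 0.8 = 56.25, so 57. That would not justify the claim either, because a constant post-baseline difference of 0.25 corresponds to a much smaller interaction effect.

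**Nothing says a null result will be read as equal efficacy.** True. That is a risk created by the overstated power, not a stated intention.

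**Conclusion.** Wrong as written. On the stated inputs, 59 per group gives 27% power, or 22% with 47 assessed, instead of 80%. The two-sided requirement is about 253 per group, or 199 if one-sided. These figures assume a continuous score, two equal independent groups, one time point and no clustering. They do not apply to the PRIME-MD diagnosis, which is binary and which the Outcome measures section names as primary.

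The planned model lifts power to about 24–47% at a single time point or 44–68% for the mean of three scores, for assumed correlations of 0.3 to 0.7. Only correlations of about 0.79 to 0.90 would reach 80%, and the article states none. The fault is confined to the CBT–PST comparison at the small difference named. The conflict between the two sample-size paragraphs is separate and needs no assumption to see.

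**What to change.** 1. Replace the d = 0.25 sentence in the second Sample size paragraph with: *For continuous depression scores, in an unadjusted two-sided comparison at one time point and ignoring clustering, 59 randomised (about 47 assessed) per arm give 80% power for d = 0.52 (0.58) and 27% (22%) power for d = 0.25 between CBT and PST.* Add the power under the planned model beside it, with the assumed correlation and the contrast stated.
2. Reconcile the two Sample size paragraphs: one power level per comparison, the effect size behind the 47, and whether 59 is before or after attrition.
3. State that CBT versus PST will be reported as an estimate with a 95% confidence interval, and that a non-significant difference will not be read as equal efficacy. For orientation, the unadjusted half-width at 47 per arm is about 0.41 SD (1.99 × √(2/47)).
4. Soften the abstract's claim that the trial will "determine which of these two interventions is most efficacious", for example to estimating the difference between the two therapies, and align the Conclusion with it.

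The cost is wording only. Enrolment, conduct and the planned model stay as they are; the published power for the head-to-head comparison becomes less favourable.
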